## Abstract

**Background:**

Morbidity before retirement has a huge cost, burdening both public health and workplace finances. Multiple factors increase morbidity such as stress at work, sedentary behavior or low physical activity, and poor nutrition practices. Nowadays, the digital world offers infinite opportunities to interact with workers. The WittyFit software was designed to understand holistic issues of workers by promoting individualized behavior changes at the workplace.

**Objective:**

The shorter term feasibility objective is to demonstrate that effective use of WittyFit will increase well-being and improve health-related behaviors. The mid-term objective is to demonstrate that WittyFit improves economic data of the companies such as productivity and benefits. The ultimate objective is to increase life expectancy of workers.

**Methods:**

This is an exploratory interventional cohort study in an ecological situation. Three groups of participants will be purposefully sampled: employees, middle managers, and executive managers. Four levels of engagement are planned for employees: commencing with baseline health profiling from validated questionnaires; individualized feedback based on evidence-based medicine; support for behavioral change; and formal evaluation of changes in knowledge, practices, and health outcomes over time. Middle managers will also receive anonymous feedback on problems encountered by employees, and executive top managers will have indicators by division, location, department, age, seniority, gender and occupational position. Managers will be able to introduce specific initiatives in the workplace. WittyFit is based on two databases: behavioral data (WittyFit) and medical data (WittyFit Research). Statistical analyses will incorporate morbidity and well-being data. When a worker leaves a workplace, the company documents one of three major explanations: retirement, relocation to another company, or premature death. Therefore, WittyFit will have the ability to include mortality as an outcome. WittyFit will evolve with the waves of connected objects further increasing its data accuracy. Ethical approval was obtained from the ethics committee of the University Hospital of Clermont-Ferrand, France.

**Results:**

WittyFit recruitment and enrollment started in January 2016. First publications are expected to be available at the beginning of 2017.

**Conclusions:**

The name WittyFit came from Witty and Fitness. The concept of WittyFit reflects the concept of health from the World Health Organization: being spiritually and physically healthy. WittyFit is a health-monitoring, health-promoting tool that may improve the health of workers and health of companies. WittyFit will evolve with the waves of connected objects further increasing its data accuracy with objective measures. WittyFit may constitute a powerful epidemiological database. Finally, the WittyFit concept may extend healthy living into the general population.

**Trial Registration:**

Clinicaltrials.gov: NCT02596737; https://www.clinicaltrials.gov/ct2/show/NCT02596737 (Archived by WebCite at http://www.webcitation.org/6pM5toQ7Y)

## Introduction

We spend one-third of our lives working. The age of retirement is regularly pushed back [1]. The main challenge in the near future will be to help workers maintain adequate health to do their work until retirement [1]. Morbidity before retirement carries a substantial public health and workplace burden. Therefore, there is a need to promote health globally, and targeting the workplace appears inherently appropriate. Current advances in technology offer infinite possibilities to interact with individuals universally. Software with the capacity to understand an individual within the context of the immediate environment seems to address this challenge. Workplace managers may benefit from advancing their understanding of the perceived well-being of the employees within their company.

The definition of health generated in 1948 by the World Health Organization remains fit for current purposes: “not merely the absence of disease or infirmity but a state of complete physical, mental and social well-being” [2]. Particularly, the role of well-being at work plays a major role in social well-being [3], and research remains limited by few large-scale investigations into physical and mental well-being in this setting. Therefore, we built a software tool based on three major health-related categories derived from the World Health Organization definition of health: physical, mental, and work-related well-being.

Taken separately, there is strong evidence between those factors and health-related outcomes but data are not typically gathered and synthesized in workplace settings. Within physical well-being, we investigate nutrition, physical activity, sleep, and musculoskeletal function. Current evidence strongly supports the benefits of a healthy diet. Multiple aspects of food intake and health have been investigated including the influence of eating breakfast [4] and the effect of excessive dietary sugars [5] and coffee [6] on heart health. The American College of Sports Medicine recommends a minimum of 150 minutes of moderate or 75 minutes of vigorous intensity of physical activity per week to achieve and maintain global health for adults and at least 30 minutes of moderate intensity physical activity per day [7]. Even a smaller amount [8] and even only standing [9,10] without substantially further increasing physical activity have shown benefits on life expectancy. Dose relationships have been identified between physical activity, life expectancy, and health benefits, even when sedentary individuals start to train more intensively after 50 years of age [11]. Therefore, any form of physical activity is better than no activity [7-9]. Similarly, shortened and prolonged sleep durations were associated with increased risk of mortality [12,13]. Also, for musculoskeletal function, the role of pain and pain-inducing musculoskeletal disorders were linked to relationships between perceived health and mortality [14]. By mental well-being, we investigate stress and mood. Stress is now considered a stand-alone risk factor for mortality [15]. Anxiety and depression are common and disabling conditions [16,17]. We investigate work-related well-being with validated and recognized models exploring work organization, job strain, latitude/decision-making, social support, and recognition [18-23].

There is also evidence demonstrating the relationships between physical, mental, and work-related well-being. This is particularly interesting for variables related to work. We will deliberately cite only the most common associations. High job strain and effort-reward imbalance seem to increase the risk of cardiovascular mortality [24]. Some working conditions, such as shift work, have been associated with abnormal eating behavior such as rescheduling of meals and eating different types of food (processed, sweets) [25], promoting an increased risk of developing obesity and metabolic disorders [26]. In addition, stress alone can facilitate unhealthy eating behaviors and the development of obesity [27]. Physical activity is a well-established coping mechanism for stress [28] and mental well-being [29]. Along with reduced workplace absenteeism [29,30], a strong negative association can exist between physical activity and mood states [31]. Working conditions are a strong determinant of morbidity [1,18,19,21,22,32-41]. For example, limited social support at work has been linked with cardiovascular events [42] and depression [43]. Deleterious, contagious effects of poor psychological working conditions are known to be associated with emotional exhaustion and depersonalization [44]. Changes in organization and subsequent conflict of loyalties resulting from work changes can lead to suicide [45]. Ultimately, stress at work is also a complex interplay with sleep [46], diet [47], and physical activity [48,49].

Because physical, mental, and work-related well-being are interconnected, a multifaceted and global understanding of individual perceptions may lead to better and more efficient preventive results. Despite the strong evidence of the benefits of stress management, diet counseling, and exercise training in patients, intervention studies on broad and representative samples of employees remain scarce. Preventive programs specific to work organizations can be implemented at the worksite [50-55]. Whereas other interventional software programs focus on specific problems such as musculoskeletal disorders [56], WittyFit aims to promote health with a holistic understanding of worker health, dynamically aligned to updated scientific knowledge (evidence-based medicine). The development of the health-promoting WittyFit software will be the first interventional study with an epidemiological cohort design that is inclusive of specific details on both leisure time and working conditions, providing a global understanding of individuals. WittyFit software will support recommendations to promote more personalized health prevention initiatives focusing on physical, mental, and work-related well-being. The shorter term hypothesis is that effective use of the WittyFit software will increase well-being and improve health-related behaviors. The ultimate hypothesis of the development of the WittyFit software is that it will increase life expectancy.

Therefore, the overall aim was to build an epidemiological database generated using Wittyfit and combining major lifestyle parameters. We aim to use these data to generate initiatives for decreasing premature mortality and morbidity in conjunction with improved well-being. WittyFit will function to generate a powerful database for strengthening the evidence and advancing knowledge on the relationships between work, behavior, and health derived from a large amount of epidemiological data.

## Methods

### Ethics

This exploratory interventional cohort study in an ecological situation received approval from the ethics committee of the University Hospital of Clermont-Ferrand, France, and has been registered at ClinicalTrials.gov [NCT02596737]. See Multimedia Appendix 1 for the original protocol.

### Participants

All workers agreeing to participate in the WittyFit study will be included from any companies willing to permit their employees to be invited to participate. The WittyFit concept follows an epidemiological design without sample size limitation. Like the Nutrinet-Santé study [57-63], the WittyFit study is never expected to end. Recruitment will commence in January 2016, and data collection will be ongoing due to the prolonged longevity of the project. Duration of participation per individual is unlimited. A staggered strategy will be to target a sample size of 200 workers from Voyages-SNCF.com within the first 6 months in order to improve and evolve the WittyFit software. WittyFit will then extend to other companies in the following year.

### Outcomes

#### Behavioral Outcomes: Three Major Health-Related Categories (WittyFit)

Workers will answer validated questionnaires within three major health-related behavioral categories: physical, mental, and work-related well-being (Textbox 1). Each main category is divided in subcategories:

Physical well-being investigates nutrition, physical activity, sleep, and musculoskeletal function. Nutrition will be assessed through 24-hour recalls of food intake. Physical activity combines questions about time spent in activity at work and leisure, as well as estimates of sedentary behavior time. This category also includes a questionnaire on sleep quality and quantity [46]. Musculoskeletal function is based on an adapted version of the Nordic Musculoskeletal Questionnaire [64].Mental well-being explores stress and mood. We will use the validated Hospital and Anxiety Depression Scale [65] and the visual analog scale of stress [66,67]. Questions on smoking and addiction will be added later.Work-related health questions explore job strain, latitude/decision-making, work organization and tasks, social support, and recognition. We will use the validated Job Demand-Control-Support model of Karasek [18-20] and the effort reward model of Sieigrist [21-23] with the addition of some specific questions such as visual analog scales (demand, control, etc) that we want to further validate.

Participants complete questionnaires at times convenient to them; however, participants will be prompted to complete a general visual analog scale from the main categories and major subcategories every 15 days and the more detailed questionnaires every 6 months. When a significant difference appears on the latest visual analog scale, the user is asked to complete specific questionnaires linked with the problem detected by the visual analog scale. Gaming and trophies are incentive strategies for workers to fulfill questionnaires.

#### Economic Outcomes and Outcomes Provided by Employers (WittyFit)

Economic data will be provided by volunteering employers from participating companies: professional roles (unskilled, skilled, mid-level workers, and senior executives), occupational sector, type of contract (full-time, part-time), absenteeism, turnover, and sales revenue and benefits. These data will be continuously updated and monitored. When a participant disappears from the database, the company will provide the relevant reason: retirement, relocation to another company, or death (premature mortality) (Textbox 1).

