### Objectives

The shorter term objectives will be to demonstrate that WittyFit improves parameters of well-being and morbidity based on three major health-related behavioral categories. The mid-term objectives will be to demonstrate that WittyFit improves economic data of the companies such as productivity and benefits. The primary long-term objective will be to demonstrate that WittyFit will contribute to decrease premature mortality.

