### Confidentiality

All medical data (medical history, treatments, etc) will be only accessible from a carefully restricted WittyFit researcher access platform. All data are anonymous, and the name of the employee is never entered into the database. The database is implemented from a human resource–generated number, which is then automatically converted into another number in the WittyFit database. Data provided by employers (such as professional roles, occupational sector, type of contract, and absenteeism) are automatically associated with the human resource–generated number.

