### Statistical Considerations

#### Sample Size Calculations

Using only Internet or computer interventions for behavior change outcomes improving eating disorders and nutrition [76], weight and cardiorespiratory fitness [77], or mood [78] and stress related to the workplace and performance and productivity [79], the sample size estimation was performed according to Cohen’s recommendations with the following defined effect size (ES) bounds: small (ES 0.2), medium (ES 0.5), and large (ES 0.8, “grossly perceptible and therefore large”) [80]. Considering an effect size of 0.33, a 2-tailed type I error fixed at a=0.001 to take into account multiple comparisons, and a moderate loss to follow-up rate, N=1000 participants will allow us to highlight (1) such ES for a statistical power greater than 95% for paired comparisons (n=225 with a correlation coefficient of .5) and (2) such ES for a statistical power greater than 80% for intergroup comparisons (n=311 by group).

For life expectancy, 100,000 workers followed over 5 years would provide a sufficient and relevant sample size to achieve the long-term objectives measured by this study. Purposive sampling will be conducted to best draw comparisons with previous research [81] studying leisure time spent sitting in relation to total mortality in a prospective cohort of US adults [9] and to further elucidate job strain among blue-collar and white-collar employees. Job strain has previously been associated with total mortality in a 28-year cohort study [82]. To address the objective of reducing premature mortality, statistical power estimation was based on a hazard ratio used for censored data (hazard ratio of 1.25 and 2) and in accordance with previously described data. This hazard ratio estimate was proposed to support a type I error of 5% (2-sided) with statistical power at 95% (see Figure 7). However, the study will be unlimited within the long-term aspects of its epidemiological design.

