#### Analyses of Longer Term Objectives

Decreased premature mortality is the long-term goal of the development of the WittyFit software. Considering this censored data, estimation will be performed as described previously using the Kaplan-Meier approach. Comparison with historical cohorts and previous research will be included in the estimates of 95% confidence intervals. WittyFit’s effect will be also studied using log-ranked comparisons and a Cox proportional hazards model. Multivariate models will be used according to univariate results and clinical and epidemiological relevance.

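### As described, the plan observes only death in service, so comparing it with historical total mortality can show a benefit even if WittyFit does nothing.

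*Protocol article*

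**What the plan says.** All references are to the protocol article.

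- **Objective.** Under Objectives: "The primary long-term objective will be to demonstrate that WittyFit will contribute to decrease premature mortality".
- **Source of deaths.** Under Economic Outcomes and Outcomes Provided by Employers: "When a participant disappears from the database, the company will provide the relevant reason: retirement, relocation to another company, or death (premature mortality". Textbox 1 repeats the same three reasons. The Abstract (Methods) gives them and concludes: "Therefore, WittyFit will have the ability to include mortality as an outcome".
- **Traceability.** Under Confidentiality: "All data are anonymous, and the name of the employee is never entered into the database". Workers are held under a converted human-resources number. No follow-up after leaving is described.
- **Analysis.** Under Analyses of Longer Term Objectives: "Considering this censored data, estimation will be performed as described previously using the Kaplan-Meier approach". Log-rank and Cox analyses are also planned, with the groups undefined.
- **External comparison.** Same section: "Comparison with historical cohorts and previous research will be included in the estimates of 95% confidence intervals".
- **Mortality studies cited.** Under Sample Size Calculations, purposive sampling is meant to allow comparison with research "studying leisure time spent sitting in relation to total mortality in a prospective cohort of US adults". The second study is introduced with: "Job strain has previously been associated with total mortality in a 28-year cohort study".

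**The concern.** Two different quantities are set side by side. By the stated route, the study sees a death only if the worker is still on the payroll. The cited research reports total mortality. A worker who becomes seriously ill, leaves and then dies is counted in total mortality but is a retirement or relocation here.

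Kaplan-Meier, log-rank and Cox methods assume that those who leave have the same later risk as those who stay. If illness drives leaving, that fails: the workforce under observation loses its highest-risk members just before their deaths, and its death rate falls. Against an external total-mortality cohort, the error favours WittyFit. With no category for illness or disability exit, the data could not show how large the problem is.

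At stake is the primary long-term claim. A large sample does not help, because it makes a biased difference more likely to reach significance.

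**Working it through.** **1. The plan's own figure.** The article proposes 100,000 workers over 5 years for hazard ratios of 1.25 and 2, at two-sided 5% and 95% power. Required deaths for equal groups (Schoenfeld) = 4(1.960 + 1.645)²/(ln HR)²: 1044 for HR 1.25 and 109 for HR 2. Over at most 100,000 × 5 = 500,000 person-years, that needs 2.09 or 0.22 observed deaths per 1000 person-years. The text gives no death rate, exit rate or group split, and Figure 7 is not shown, so 100,000 can be neither confirmed nor refuted. The deaths that count are those the employer records.

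**2. Leaving unrelated to health.** Assume a constant death rate of m = 0.002 per year and leaving at rate l. Share of 5-year deaths seen = [m/(l+m)](1 − e^(−5(l+m)))/(1 − e^(−5m)).
- l = 0.15: 70% of deaths seen.
- l = 0.40: 43% of deaths seen.

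The observed rate ratio is 1.00 in both, because leavers take their person-time with them. The share of deaths captured is therefore not the bias.

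**3. Leaving driven by illness.** Assumed rates, none from the document: death 0.001 per year if well, illness onset 0.005, death 0.150 once ill, extra leaving of the ill at x per year, 5 years, no WittyFit effect. Let R be the ratio of ill to well workers still employed:

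- dR/dt = 0.005 − kR, with k = 0.150 + x − (0.001 + 0.005) = 0.144 + x
- mean R over 5 years = (0.005/k)[1 − (1 − e^(−5k))/(5k)]
- mean death rate ≈ (0.001 + 0.150·R)/(1 + R)

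| x per year | mean R | rate per 1000 | ratio to true |
|---|---|---|---|
| 0 (true total mortality) | 0.00997 | 2.47 | 1.00 |
| 0.10 | 0.00865 | 2.28 | 0.92 |
| 0.25 | 0.00715 | 2.06 | 0.83 |
| 0.50 | 0.00545 | 1.81 | 0.73 |
| 1.0 | 0.00361 | 1.54 | 0.62 |

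Step-by-step integration gives the same ratios (rates 2.46, 2.27, 2.05, 1.81 and 1.53).

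**4. Ordinary turnover.** Turnover that is equal for well and ill cancels out of R, so an estimate at a given follow-up time is unaffected (ratio 1.00). A crude rate per person-year still falls, to 2.36/2.46 = 0.96 with 10% turnover, because observed time shifts to early years when few have become ill. With 10% turnover plus x = 0.10 to 1.0, the crude ratio is 0.89 to 0.62.

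**5. Chance of a false benefit.** One-sample Poisson test, lower 2.5% tail, assumed historical rate of 2 per 1000. Person-years run from 500,000 (no loss) to 350,000 (about 70% retained, as with 15% turnover).
- 500,000: 1000 deaths expected, benefit declared at 937 or fewer.
- 350,000: 700 expected, benefit declared at 648 or fewer.

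| Ratio with no true effect | 350,000 | 500,000 |
|---|---|---|
| 1.00 | 2.5% | 2.3% |
| 0.95 | 26% | 34% |
| 0.90 | 77% | 89% |
| 0.80 | about 100% | about 100% |

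**6. Internal comparisons.** If the ill leave at 0.25 per year in one group and 0.10 in the other, the apparent ratio is 2.05/2.27 = 0.90, or 2.27/2.05 = 1.11 with the groups reversed. The direction depends on which group loses its ill workers faster.

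**The case against.** Several points on the other side carry weight.

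- **Censoring of leavers is not stated outright.** It is inferred from the reference to censored data and from the absence of any later data on leavers. This stands as a caveat. No other handling is described.
- **The exit list may not be complete.** The Abstract calls the three reasons major explanations, and the full protocol in Multimedia Appendix 1 is not shown. It might hold more codes or a vital-status linkage. The Abstract nevertheless rests the mortality outcome on the employer's record.
- **The comparator is loosely identified.** The analysis section does not name its historical cohorts. The two total-mortality studies appear under sample size, as associations with sitting and job strain. Whether they followed people regardless of employment cannot be told from the article. Comparing associations within cohorts need not favour WittyFit.
- **The size rests on assumptions.** The ratio of 0.62 needs ill workers to leave at 1.0 per year. Differences in age, country or period could offset the bias as well as add to it.
- **The study is labelled exploratory** and also plans log-rank and Cox analyses. That limits the claim, but the stated long-term aim is still to demonstrate lower mortality.

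A reader might infer that a false benefit is certain, or that the apparent hazard ratio equals the share of deaths captured. Neither holds: 43% to 70% of deaths can be captured with a ratio of 1.00. Nor do the objectives include keeping ill workers employed; staying healthy enough to work until retirement is background in the Introduction.

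**Conclusion.** The point holds in conditional form. By the only route described, the study observes death in service, and it plans to set this against historical cohorts and previous research, where the mortality studies it cites concern total mortality. If ill workers leave before dying, the comparison can show a benefit with no effect; internal Cox comparisons can err either way.

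Under the assumed rates, the ratio is 0.92 to 0.62 for illness-driven leaving at 0.10 to 1.0 per year. It is 0.96 on a crude person-year basis with 10% ordinary turnover alone, and 1.00 for an estimate at fixed follow-up time when leaving is unrelated to health. At the planned size a small deficit is enough: 0.95 gives a 26-34% chance of a falsely significant benefit and 0.90 gives 77-89%, against a nominal 2.5%. These figures show sensitivity and do not predict the result. The short-term and mid-term objectives do not depend on this point.

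**What to change.** 1. Add two employer exit codes: one for ill-health or disability exit, and one for resignation, dismissal or contract end.
2. Ascertain vital status after leaving. If that is not done, name the endpoint death in service and limit the claim to it.
3. Report a sensitivity analysis of the composite of death or ill-health exit.
4. Use historical total-mortality cohorts descriptively only, or compare only with cohorts that use the same in-service definition.

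A competing-risk estimator should not be offered as a cure. Leaving a job does not prevent death. A cause-specific Cox model that treats exits as competing events gives the same hazard ratio as the planned one, and a cumulative incidence curve recovers no death after exit.

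The cost is two extra codes on the employer form and, without vital-status follow-up, a narrower mortality claim. The codes should be added early: recruitment is open-ended, and exit reasons not recorded at the time may be impossible to recover.
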